### Covariates

The following covariates will be accounted for when analyzing the results: sex, age, socioeconomic status, estimated general intelligence (WP7), executive function (WP7) and early developmental difficulties as described in WP8.

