### Objectives to be explored in the RCT

1. To estimate the effect of a motor skills intervention on language and pre-literacy development in preschool children

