### Covariates

The following covariates will be accounted for when analysing the results: Sex, age, socioeconomic status, motor development.

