### Objectives to be explored in the RCT

The objective is to estimate the effect of a motor skills intervention on wellbeing.

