### Variables

*Predictors:*

- Motor skills as described in the main application
- Physical activity as described in WP 4

*Outcomes:*

Psychological wellbeing will be measured using the Strengths and Difficulties Questionnaire (SDQ) [7- 9]. The SDQ is a brief questionnaire measuring child and adolescent psychological wellbeing. The SDQ includes 25 items, divided into 5 scales (5 items each): 1) emotional symptoms, 2) conduct problems,

3) hyperactivity/inattention, 4) peer relationship problems and 5) pro-social behavior. The SDQ further includes an impact supplement that asks if the registered behavior is considered a problem and if overall distress, social impairment, burden and chronicity are experienced. The SDQ is widely used to screen for mental health difficulties and as an outcome measure of psychological wellbeing both in clinical practice and in research. A total difficulties score is generated by adding scales 1-4 together and has been found to function as a dimensional measure of child mental health [10]. The questionnaire is available for parent and teacher reporting of children in four different age groups: toddlers (age 2 to 4 years), preschool children (age 5 to 6 years), school children (age 4 to 10 years) and adolescents (age 11 to 17 years). A self-report version is available for adolescents (age 11 to 17 years) [8]. All questionnaires are available in Danish and normative data from Denmark is available for children aged 5 to 12 years [11].

In the RCT, parental and staff reporting will be sampled. The use of multiple informants is commonly recommended to provide the most complete picture of the child’s psychological wellbeing and mental health, as parents and teachers observe children in different contexts, where different behaviors may be exhibited by the child [12]. For the cohort study, the self-report questionnaire is added when the children are aged 11 years or older. The SDQ will be administered electronically to parents and preschool staff twice yearly during preschool and to parents and teachers annually throughout the school years, with the addition of the self-report questionnaire when the child is 11 years of age and older.

The SDQ is expected to take around 10 minutes to complete.

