Wellbeing is further measured using the KINDLR [13]. The KINDLR is a generic instrument for assessing health-related quality of life in children and adolescents (age 3 to 17 years). The KINDLR consists of six subdomains, each with four items. In this study, the subscales on physical wellbeing, emotional wellbeing and self-esteem are included (total of 12 items). During preschool, the KiddyKINDL-parents (age 3 to 6 years old) are used. Later, respective of age, parents’ report on the KiddyKINDL or the Kid- kiddoKINDL (age 7 to 17 years old), and children and adolescents report on the KidKINDL (age 7 to 13 years old) or the KiddoKINDL (age 14 to 17 years of age). Danish versions for children and adolescents age 7-17 are freely available. A Danish version of the KiddyKINDL- parents will be made following the instructions provided by the authors. The KINDLR will be administered at baseline and at follow-up as specified in the main protocol. The 12 KINDLR items are expected to take around 5 minutes to complete

The primary outcomes used for analyses in the RCT will be:

- Parent-reported psychological wellbeing, total difficulties score

Secondary outcomes used for analyses in the RCT will be:

- Staff-reported psychological wellbeing, total difficulties score
- Parent-reported wellbeing, total of physical and emotional subscale
- Parent-reported self-esteem

In the cohort study, the following outcomes will be added.

- Self-reported psychological wellbeing, total difficulties score*
- Self-reported wellbeing, total of physical and emotional subscale**
- Self-reported self-esteem**

* For children aged 11 years and older

** For children aged 7 years and older

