**Objectives**

1. To investigate whether a motor skills intervention improves the preschool children’s executive functioning, especially in terms of self-control and inhibitory control.
2. To investigate the effect of a motor skills intervention on academic performance.

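### WP6 lists as a covariate for all results a WP8 status that is partly recorded after randomisation and partly built from the SDQ, and its RCT model text does not settle whether that status enters

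*Protocol*

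**What the plan says.** WP6 has an RCT objective: "The objective is to estimate the effect of a motor skills intervention on wellbeing". Its primary RCT outcome is "Parent-reported psychological wellbeing, total difficulties score"; the staff-reported version is one of the secondary outcomes. The instrument is repeated after baseline: "The SDQ will be administered electronically to parents and preschool staff twice yearly during preschool".

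The WP6 Covariates section opens with "The following covariates will be accounted for when analyzing the results: sex, age, socioeconomic status, estimated general intelligence (WP7" and closes with "executive function (WP7) and early developmental difficulties as described in WP8". It gives no time point and does not separate the RCT from the cohort study, although the WP6 sections on objectives, outcomes, length of follow-up and analyses all do.

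WP8, Variables, treats a child as being at early developmental risk if any of these is met:

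- a psychiatric diagnosis, received before or in the course of the project;
- a pervasive medical diagnosis, received in the course of the project;
- an SDQ algorithm result from the parent or the staff form, with no date attached;
- a high level of concern from staff while the RCT is running.

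The WP6 Analyses section describes the RCT model as containing the baseline outcome, time since baseline, group and any imbalanced covariates, with preschool and area socioeconomic status as random effects. It does not mention the covariate list.

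**The concern.** An RCT effect model should adjust only for what was fixed before the intervention could act. A status that the intervention can change, and that is partly computed from the outcome instrument, fails that test. If fewer intervention children are flagged because their SDQ scores improve, holding the flag constant hides part of that improvement. Conditioning on a post-randomisation variable can also bring in bias from unmeasured causes that it shares with the outcome, in a direction that cannot be fixed in advance.

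At stake is the WP6 effect estimate on wellbeing: a real but modest benefit could be under-reported. Two other covariates raise a lesser question of the same kind. Executive function in WP6 has no date, yet WP7's first objective begins "To investigate whether a motor skills intervention improves the preschool children" and concerns executive functioning. In WP5 the list reads "The following covariates will be accounted for when analysing the results: Sex, age, socioeconomic status, motor development", while that work package has the RCT objective "To estimate the effect of a motor skills intervention on language and pre-literacy development in preschool children".

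**Working it through.** **Step 1: can the WP8 status be read as a baseline variable?**

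| Route into the status (WP8, Variables) | When it can be met | Shares content with a WP6 RCT outcome? |
|---|---|---|
| Psychiatric diagnosis | before or during the project | no |
| Medical diagnosis | during the project | no |
| SDQ algorithm, parent or staff | undated; SDQ collected twice yearly | yes |
| Staff concern | during the RCT | no |

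Three of the four routes expressly reach into the project or RCT period, and the fourth is undated on a repeated instrument. No baseline-only version is defined. WP8 also defines developmental difficulties as an outcome, with the SDQ taken at the last data collection; reading the WP6 covariate that way would place it later still.

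**Step 2: how far does it overlap the outcome?** WP6 builds total difficulties from four scales: emotional, conduct, hyperactivity and peer problems. The WP8 algorithm uses SDQ symptom and impact scores to rate conduct, emotional, hyperactivity and any disorder. The overlap is substantial but not complete.

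**Step 3: does the RCT model text settle it?** The Covariates section says the listed variables will be accounted for. The Analyses section admits only imbalanced ones. WP1 speaks of imbalance in baseline covariates; WP6 does not repeat the word baseline for this rule. If imbalance were checked on the WP8 status as defined, an effective intervention could itself create the imbalance that triggers adjustment.

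**Step 4: illustrative size.** The document gives no effect size, SD or sample size for this outcome, so every input here is an assumption: effect *d* = 0.20 or 0.30 SD, baseline to follow-up correlation *r* = 0.5 or 0.7, and 5, 10 or 20% of children above the SDQ cut at any one wave without intervention. The simulation used 1,000,000 children, one informant and ordinary least squares without clustering.

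- Baseline score: b ~ N(0,1).
- Final score: y = r·b + √(1−r²)·e − d·group.
- Intermediate wave: w = r·b + √(1−r²)·(0.5·e + √0.75·e′) − d·group.
- Any-wave status: 1 if b, w or y exceeds the cut.
- Models: y on group and b, then the same with the status added. Loss = 1 − (adjusted effect / unadjusted effect).

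| r | Above cut | d = 0.20: without → with status | d = 0.30: without → with status |
|---|---|---|---|
| 0.5 | 5% | −0.200 → −0.179 (10% lost) | −0.300 → −0.271 (10%) |
| 0.5 | 10% | −0.200 → −0.167 (17%) | −0.300 → −0.254 (15%) |
| 0.5 | 20% | −0.203 → −0.155 (24%) | −0.300 → −0.234 (22%) |
| 0.7 | 5% | −0.202 → −0.189 (6%) | −0.301 → −0.284 (6%) |
| 0.7 | 10% | −0.200 → −0.179 (11%) | −0.301 → −0.273 (9%) |
| 0.7 | 20% | −0.201 → −0.168 (17%) | −0.300 → −0.256 (15%) |

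A status cut from the final wave alone lost 10 to 39% over the same grid. A status from the baseline score alone lost 0% in every row.

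The simulated flag is a cut on the outcome score itself, a closer overlap than the real algorithm would give. On the other hand, it uses two follow-up waves and one informant, where the plan has twice-yearly SDQ from two. Diagnoses and staff concern were not modelled.

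**The case against.** The strongest reply is that the only text describing the WP6 RCT model does not force the listed covariates in. It admits imbalanced ones, WP1 ties imbalance to baseline, and WP6 refers back to the WP1 covariate work in its drop-out paragraph. On that reading the WP8 status need never enter. This has weight: the document does not say outright that the status goes into the RCT model. But the Analyses section neither overrides nor mentions the Covariates section, and a status without a baseline version cannot be checked for baseline imbalance. The two sections remain unreconciled.

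Stronger readings are tempting, and the document does not support them:

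- A reader might infer that the outcome is adjusted for itself. The flag and the total score overlap but differ, and two of the three secondary RCT outcomes come from another instrument, the KINDL-R.
- A reader might infer that executive function is a post-baseline mediator in WP6. It is only undated. WP7 enters the baseline value of executive functioning in its own model, so a baseline measure is planned, and adjusting for that is harmless.
- A reader might infer that WP5 adjusts away its own effect, for instance from 0.3 × 0.4 = 0.12 SD to zero. That result needs an RCT model that WP5 does not describe, a follow-up motor score, and no direct effect of the intervention on language. The WP5 Analyses section describes association and prediction models, where motor development belongs.
- A reader might take shrinkage toward zero as certain. Bias from unmeasured shared causes could run either way.

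**Conclusion.** The concern holds for the WP8 status in WP6. As written, the covariate list applies to all WP6 results a variable that is partly ascertained after randomisation and overlaps the primary and one secondary RCT outcome, and the RCT model text does not clearly exclude it. If followed, the adjustment would be expected to remove part of any true effect: about 6 to 24% for a status met at any wave, conditional on the assumed inputs above, against none for a baseline-only status. The document itself supplies no figure for the loss.

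For executive function in WP6 and motor development in WP5, the fault is an unstated time point and no more. Severity is moderate, because the issue bears on a work-package outcome and leaves the WP1 primary outcome untouched.

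**What to change.** In WP6, Covariates and Analyses, state that RCT effect models adjust only for values measured before the intervention starts, and say how the covariate list relates to the rule on imbalanced covariates. Either leave the WP8 status out of those models, where the baseline SDQ already enters as the baseline value of the outcome, or define a version from baseline data only. Specify baseline executive function. Keep the post-baseline status for the cohort analyses or a separate mediation analysis.

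As a minor matching edit in WP5, Covariates, state that any RCT effect model uses baseline motor skills only; motor development stays as the exposure in the association models.

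The cost is a few sentences. No data collection changes and no data are lost: the SDQ and executive function are planned at baseline, and parents report diagnoses at baseline.

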### Length of follow-up

For the RCT the follow-up period will be 6 to 30 months, which covers the period from the beginning of the intervention until the last measurement before the child leaves preschool (see Figure 1 in the main protocol). For the cohort study, the duration of the follow up will be 12 years, which covers three years in preschool and nine years in school.

### Analyses

For the RCT study, multilevel linear regression models will be constructed to assess the effectiveness of the intervention on psychological wellbeing. The baseline value of the outcome variable, time since baseline, intervention group and any imbalanced covariates will be added to the model along with preschool and socioeconomic status of the area as random effects. The interaction between preschool and intervention group will be tested. The assumptions for the models will be checked. Similar multilevel linear regression models will be constructed for both the child’s physical and emotional wellbeing and self-esteem. Measures for both groups at baseline and at following points of data collection will be further analyzed using linear mixed effects models (random coefficient models and multilevel models).

The above analyses will be repeated on the children who were considered to have a ‘poor’ level of motor skills at baseline.

In addition to the WP1 analysis of the covariates, an analysis will be conducted to determine if the children who dropped out of the study were different from those who remained, based on the baseline values of the outcome variables.

For the cohort study, longitudinal latent class analysis and latent class growth analysis will be conducted to describe the developmental patterns of wellbeing.

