## Analyses of effect

Simple univariate statistics will be used to describe the outcomes and covariates by preschool. Bivariate analysis adjusted for the design effect will be done to determine if there were any imbalances in the baseline covariates among the two groups.

Multilevel linear regression models will be constructed to assess the effectiveness of the intervention on motor skill performance. The baseline value of the outcome variable, time since baseline, intervention group and any imbalanced covariates will be added to the model along with preschool and socioeconomic status of the area as random effects. The interaction between preschool and intervention group will be tested. The assumptions for the models will be checked.

Multilevel ordinal regression models will be constructed to assess the effectiveness of the intervention on the parents’ perception of their child’s motor competence. The baseline value of the parents’ perception, time since baseline, intervention group and imbalanced covariates will be independent variables. The school and socioeconomic status of the area will be entered as random effects and the interaction between school and intervention will be tested. The model’s assumptions will be tested.

The above analyses will be repeated on a subsample of children who were considered to have a ‘poor’ level of motor competence at baseline.

An analysis will be conducted to determine if the children who dropped out of the study were different from those who remained, based on the baseline values of the outcome variables and the covariates.

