## Perspectives

The Svendborg City Council has granted generous resources to educate the staff; the staff at the preschools is eager to participate; the preschool teachers have contributed to the design of the intervention, ensuring a sense of ownership and involvement; and there is experience with conducting large, cluster randomised controlled trials in the Municipality. Therefore, the conditions for implementation of the intervention in the preschools are optimal. Consequently, if we cannot show an improvement in the children’s motor skills using this framework, further allocation of resources to programs to improve motor development in preschools should probably be discontinued.

On the other hand, if the intervention does succeed, the program can easily be applied in other Danish municipalities due to the design, where each preschool applies the intervention principles in a way to suit their individual conditions regarding physical environment, staffing, etc.

Finally, if the intervention improves motor competence in the children with the highest need for improvement, targeted interventions could be considered if, in some settings, prioritizing of resources is necessary.

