A prophylactic strategy focusing on improving motor skills activities in preschool children may therefore have the potential to improve the current and future physical, psychological and social wellbeing and their associated health benefits. Based on previous research on poor motor skills and wellbeing, the effect of motor skills training may be stronger for children who are initially characterized by poor motor skills.

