### Perspectives

Increased knowledge of the role of motor skills in the development of wellbeing and insight into the protective potential of early motor skills training could aid in both the future development of high quality preschool care and more specifically target interventions for children with poor motor skills.

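### WP 6 expects a stronger effect in children with poor motor skills, but WP 6 and WP 1 only repeat the models in that subsample, which cannot show a larger effect

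*Protocol*

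**What the plan says.** The Background to WP 6 states that "the effect of motor skills training may be stronger for children who are initially characterized by poor motor skills". The WP 6 trial objective is narrower: "The objective is to estimate the effect of a motor skills intervention on wellbeing". The primary trial outcome in WP 6 is listed as "Parent-reported psychological wellbeing, total difficulties score".

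The Analyses section of WP 6 fits multilevel linear models to all children. It then says "The above analyses will be repeated on the children who were considered to have a" 'poor' level of motor skills at baseline. The Analyses of effect section of WP 1 does the same: "The above analyses will be repeated on a subsample of children who were considered to have a" 'poor' level of motor competence at baseline. The one interaction with intervention named in WP 6 is this: "The interaction between preschool and intervention group will be tested". WP 1 names the same one.

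Both packages say what the subgroup results might be used for. WP 1, Perspectives: "if the intervention improves motor competence in the children with the highest need for improvement, targeted interventions could be considered", with the added condition that resources have to be prioritised in some settings. WP 6, Perspectives, hopes that the knowledge gained could help to "more specifically target interventions for children with poor motor skills".

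**The concern.** 'Stronger' is a comparative word. It means stronger than in the children whose motor skills are not poor. An analysis confined to the poor-skill children has no comparator, so it cannot address that expectation whichever way it comes out. A significant result in the subsample is compatible with an equal effect in everyone. A non-significant one is compatible with a larger effect estimated from too few children.

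At stake is how the results will be read. With a stated expectation of a stronger effect and a subsample result beside it, a report could easily present the latter as evidence for the former, although nothing in the plan would support that step.

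**Working it through.** **1. What each analysis estimates.** Write d_P for the effect in poor-skill children, d_O for the effect in the others, and s for the share of poor-skill children.
- The WP 6 expectation is d_P − d_O > 0.
- The subsample model estimates d_P only.
- The full-sample model estimates roughly s·d_P + (1−s)·d_O.
- Setting the two side by side gives d_P − [s·d_P + (1−s)·d_O] = (1−s)(d_P − d_O). This is a shrunken version of the contrast, from overlapping data, with no planned standard error.

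Only an interaction term estimates d_P − d_O directly, with a confidence interval.

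**2. Is such a term planned elsewhere?** In WP 1 and WP 6 the only interaction with intervention is with preschool. WP 3 has an interaction of time with poor motor performance, but in a cohort analysis of movement patterns and without an intervention term. So none is planned for this question.

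**3. Illustration of the inference problem** (all inputs assumed; the document gives none). Take the same true effect of 0.3 SD in both groups, 800 children, 25% poor, 20 preschools, intracluster correlation (ICC) 0.02, two-sided alpha 0.05.
- Poor-skill children per arm: 800 × 0.25 / 2 = 100, or 10 per preschool.
- Design effect: 1 + 9 × 0.02 = 1.18; effective number per arm 100 / 1.18 = 84.7.
- Standard error: √(2 / 84.7) = 0.154; 0.3 / 0.154 = 1.95; power about 50%.

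The subsample test is therefore significant in about half of such trials although the effect is no larger in poor-skill children. More children would raise that proportion, not lower it.

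**4. Precision of the subsample.** Before clustering, its standard error is 1/√s times that of the full sample: 4.5, 2.6 and 2.0 times for assumed shares of 5%, 15% and 25%. What this means for power depends on quantities that the document does not state:
- With 80% power overall, a uniform effect and clustering ignored, subgroup power is Φ(2.80·√s − 1.96): 9%, 19% and 24% for shares of 5%, 15% and 20%.
- Ignoring clustering overstates the loss if allocation is by preschool, because the subset has fewer children per preschool. With 40 children per preschool and a 15% share (6 per preschool), ICC 0.02 gives 0.15 × 1.78 / 1.10 = 0.243 of the full information, and power Φ(2.80 × √0.243 − 1.96) = 28%. ICC 0.10 gives 0.15 × 4.9 / 1.5 = 0.49, and power 50%.
- With total sample size left free (400 to 1,500 children, 20 preschools, share 5% to 25%, ICC 0.02 or 0.10), subgroup power is 10–70% for an effect of 0.3 SD and 20–99% for 0.5 SD.

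So precision is lower than in the full sample, by an amount that cannot be fixed here.

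**5. What the interaction would deliver.** With baseline skill split into poor and other, the interaction standard error is 1/√(1−s) times that of the subsample before clustering: 1.03, 1.08 and 1.15 for shares of 5%, 15% and 25%. In the best case, where preschool effects cancel, power for a 0.3 SD difference in effect over shares of 5% to 25% is 10–25% with 400 children, 15–45% with 800 and 24–71% with 1,500. It answers the right question, but not with high power.

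**The case against.** The best defence is that the plan never promises to demonstrate effect modification. The expectation is one Background sentence worded with 'may', the stated objective is the overall effect, and the Analyses section does not say that the repeat analysis tests the expectation. This stands as far as it goes: it is an expectation, not a formal hypothesis. Yet the repeat is the only analysis that bears on it.

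Second, WP 1 ties targeting to improvement in the neediest children where resources are limited. That condition is benefit within the group, not greater benefit than in others, and a subgroup estimate does inform it. This stands. A programme that helps everyone equally would give a null interaction, and targeting by need could still be defended.

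Third, an interaction could be specified in a statistical analysis plan that is not shown. But the protocol itself sets out how these children will be analysed and names interactions where it wants them, so this is a method chosen, not a detail deferred.

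Two stronger readings are tempting. A reader might infer that the subgroup analysis has very little power. The document gives none of the inputs, and assumed inputs take power from very low to ample. A reader might also infer that the plan will judge targeting by comparing significance between poor-skill and other children. No such comparison is planned, and no separate analysis of the other children is described.

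**Conclusion.** The point holds as a mismatch between the expectation in WP 6 and the method given in WP 6 and WP 1. The planned subsample analysis estimates the effect in poor-skill children and cannot show that it is larger than in other children. That conclusion needs no assumption about sample size, clustering or the share of poor-skill children. The accompanying loss of precision is real in direction but cannot be sized from this document; every power figure above rests on assumed inputs. The overall analyses in both packages are unaffected, and estimating the effect within poor-skill children is legitimate in itself.

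**What to change.** In WP 1 and WP 6, add to the model fitted to all children an interaction between intervention and the baseline MABC-2 score, kept continuous. From that model, report the intervention effect with its 95% confidence interval at a 'poor' and at an average baseline level. State that any claim of a stronger effect in poor-skill children will rest on the interaction estimate and its interval. Keep the within-subgroup estimate, labelled as the answer to whether these children benefit.

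The cost is small. The WP 1 motor-skill model already includes the baseline value of its outcome, so it needs one further term. The WP 6 models and the WP 1 parent-perception model adjust for the baseline of their own outcomes, so they need the baseline MABC-2 main effect as well as the interaction. One sentence per package covers it, and no new data are needed, because baseline motor skill must already be known to identify the 'poor' group. The continuous term assumes a roughly linear change in effect over the score, which should be checked along with the other model assumptions. The downside is that the interaction estimate will be imprecise and may be inconclusive; the change corrects the question answered, not the power.
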